### Primary aim

This article presents the rationale and protocol development for a research project aimed at evaluating the effects of a mindfulness-based meditation intervention on quality of life, sleep, and mood in adolescents with cancer compared to a control group. In light of data available on adult populations and emerging from research in youth, three hypotheses are formulated: (1) mindfulness meditation will have beneficial effects on the mood of adolescents completing this practice; (2) mindfulness meditation will have beneficial effects on quality of life of the participants; and (3) mindfulness meditation will have beneficial effects on sleep quality of the participants.

Specifically, significant improvements are expected to be observed in quality of life, mood, and sleep between pre-intervention and post-intervention measures in the experimental group. These effects should be sustained 6-months post-intervention.

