### Primary outcome measures

Beck Youth Inventories™ - Depression and anxiety scales
[41]: this measure will be used to evaluate symptoms of depression and anxiety. Each scale comprises 20 items, for which participants are asked to indicate on a Likert-type scale ranging from 0 (‘never’) to 3 (‘always’) how frequently each statement applied to them in the past two weeks. Both scales have presented excellent internal consistency (α >0.84) and good reliability (r >0.73) for adolescent populations
[42]. For the purposes of this project, a validated French version will be used
[43].

Positive and Negative Affect Schedule - Child (PANAS-C)
[44]: this measure is used to evaluate the presence and fluctuations in positive and negative emotions. The questionnaire comprises 20 items, for which participants are asked to answer on a Likert-type scale ranging from 1 (‘not much or not at all’) and 5 (‘a lot’), whether the described emotion matches what they have felt like in the past few weeks. This measure presents excellent results in terms of internal consistency (α ranging from 0.91 to 0.92) and good reliability for adolescent populations
[45]. A French version has been validated, and will be used for this project
[46].

Pediatric Cancer Quality of Life Inventory
[47]: this measure is used to evaluate quality of life in children and adolescents with cancer. The questionnaire comprises 27 items for which participants are asked to indicate on a Likert-type scale ranging from 0 (‘never’) to 4 (‘almost always’) how much each symptom has been problematic in the past month. The measure has good to excellent psychometric properties in terms of construct validity, reliability, internal consistency (α = 0.91 to 0.92) and clinical validity
[47]. A French version of this questionnaire is available and will be used for this project
[48].

Pittsburgh Sleep Quality Index
[49]: this measure evaluates sleeping habits in the past month. The questionnaire comprises 11 items, and presents good psychometric properties in terms of internal consistency (α = 0.83), test-retest reliability (r = 0.85), and convergent validity
[49]. This measure is commonly used with adolescents and is validated in French
[50-52].

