### Planned statistical analyses

Descriptive statistics on participant characteristics will be presented for each group at baseline. Means and standard deviations on primary and secondary outcome variables will be presented for each group at 8 weeks and 6 months.

The cut-point to reject the null hypothesis will be set at 5% (α ≤0.05). Primary hypotheses will first be tested using three mixed analyses of covariance (ANCOVA) with Bonferonni corrections and individual critical alpha levels at 1.67% (α ≤0.0167), that will allow comparison of data at each time-point
[54]. The use of mixed ANCOVAs will help reduce within-group error variance, namely by controlling for baseline differences between participants in each condition and by taking into account possible confounds (for example, age, diagnosis, cancer stage), while providing a higher statistical power in detecting an intervention effect (
[55,56]).These intra-group analyses will serve to evaluate the impact of the mindfulness-based meditation intervention on quality of life, sleep, and mood pre-post intervention, as well as follow-up.

Specifically, changes in quality of life scores (as indicated by the Pediatric Cancer Quality of Life Inventory) between baseline, 8 weeks and 6 months will be tested. Similarly, a change in sleep quality scores (as indicated by the Pittsburgh Sleep Quality Index) and mood scores (as indicated by the Depression and anxiety scales of the Beck Youth Inventories and the PANAS-C) will be tested between baseline, 8 weeks and 6 months. These analyses will also serve to test secondary hypotheses, by allowing inter-group comparisons between the experimental group and the wait-list controls. Specifically, a difference in quality of life scores, sleep quality scores, and mood scores at baseline, 8 weeks, and 6 months will be assessed between groups.

Comparable analyses will be conducted on the data collected from the second experimental group once participants from the wait list condition go through the intervention. All statistical analyses will be conducted using SPSS version 20 (SPSS Inc., Chicago, IL, USA).

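### Three ANCOVAs at 0.0167 do not match the five or six primary scores listed, so the 5% level is not guaranteed

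*Protocol article*

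**What the plan says.** Planned statistical analyses sets the significance level: "The cut-point to reject the null hypothesis will be set at 5% (α ≤0.05"). It continues that the primary hypotheses will be "tested using three mixed analyses of covariance (ANCOVA) with Bonferonni corrections and individual critical alpha levels at 1.67" percent, that is 0.0167. The number three agrees with Primary aim, where "three hypotheses are formulated: (1) mindfulness meditation will have beneficial effects on the mood of adolescents completing this practice", followed by quality of life and sleep.

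The same analysis section assigns one instrument to quality of life (the Pediatric Cancer Quality of Life Inventory) and one to sleep (the Pittsburgh Sleep Quality Index). For mood it refers to "mood scores (as indicated by the Depression and anxiety scales of the Beck Youth Inventories and the PANAS-C").

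Primary outcome measures lists all of these instruments as primary. Of the two 20-item Beck scales it says that "this measure will be used to evaluate symptoms of depression and anxiety". Of the PANAS-C it says that "this measure is used to evaluate the presence and fluctuations in positive and negative emotions". It does not say whether the PANAS-C gives one score or two.

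**The concern.** The Bonferroni divisor counts domains, and one of the three domains holds several scores. A univariate ANCOVA analyses one dependent variable, so a single mood ANCOVA needs a single mood variable. The article lists three or four candidates and does not say which one, or what combination, enters the model.

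The natural way to run the text as it stands is one model per score, each read at 0.0167. Mood then gets three or four chances at a threshold meant for one, and a chance result on any of them could be presented as a benefit on mood. The article says that the results may help decide which variables go into later trials, so mood could be carried forward ahead of sleep or quality of life only because it was tested more often.

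**Working it through.** **Inputs from the protocol article**
- Significance level 0.05, three ANCOVAs, 0.0167 each (Planned statistical analyses).
- Quality of life: 1 score. Sleep: 1 score. Mood: Beck depression, Beck anxiety and PANAS-C, so 3 scores, or 4 if positive and negative affect are separate (Planned statistical analyses; Primary outcome measures).

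**Inputs assumed**
- One test per score, each read at 0.05/3. This is inferred.
- Correlations between test statistics of 0.5 to 0.7 within mood and 0.3 to 0.5 across domains. The document gives none.

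**Step 1. The plan's own figure.** 0.05/3 = 0.01667, which rounds to 0.0167. It reproduces. With three tests the upper bound is 3 × 0.01667 = 5.0%, and under independence the rate is 1 − (1 − 0.01667)³ = 4.9%. The arithmetic is right for three tests.

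**Step 2. Count of listed scores.** 1 + 1 + 3 = 5, or 1 + 1 + 4 = 6.

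**Step 3. Chance of at least one false positive over all scores.** The bound is k × 0.05/3. Under independence the rate is 1 − (1 − 0.05/3)^k. The correlated case uses two-sided normal test statistics; its lower end is the 0.7/0.5 pair (within mood/across domains) and its upper end the 0.5/0.3 pair.

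| Scores | Bound | Independent | Assumed correlations |
|---|---|---|---|
| 3 (as stated) | 5.0% | 4.9% | not needed, bound is 5% |
| 5 | 8.3% | 8.1% | about 6.3% to 7.3% |
| 6 | 10.0% | 9.6% | about 7.1% to 8.4% |

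**Step 4. Mood alone, against its 1.67% share.**

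| Mood scores | Independent | Correlation 0.7 to 0.5 within mood |
|---|---|---|
| 3 | 1 − (1 − 0.01667)³ = 4.9% | about 3.9% to 4.5% |
| 4 | 1 − (1 − 0.01667)⁴ = 6.5% | about 4.8% to 5.7% |

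**Step 5. When would 5% hold anyway?** With one common correlation between all test statistics, the overall rate falls to 5% at about 0.77 for five scores and about 0.82 for six. It also holds, at any correlation, if mood is tested through one prespecified score or composite, or if a mood claim requires every mood score to be significant. The article states none of these.

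**Step 6. Thresholds that match the count.** 0.05/5 = 0.0100 and 0.05/6 = 0.0083. Splitting only mood's share gives 0.01667/3 = 0.0056 or 0.01667/4 = 0.0042.

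**The case against.** The article never says that each mood score gets its own test at 0.0167, nor that one significant mood score would be enough. It says three analyses for three hypotheses, and one named score or one composite would make that exactly right. Questionnaire scoring and the rule within a domain are also details that a journal article often leaves to a fuller plan.

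This limits the point in three ways.
- A reader might infer that the 5% level is simply false. The document does not support that: very high correlation, a composite or an all-significant rule would hold it. What can be said is that 5% is not guaranteed.
- A reader might infer that three ANCOVAs cannot be run and that five or six are required. That goes too far as well: three are possible once the mood variable is fixed.
- The size depends on assumed correlations and on unstated PANAS-C scoring, so the figures for three mood scores belong beside those for four.

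The objection does not remove the point. The article is not silent here: it fixes a number of tests and a threshold, and its own list of primary measures does not fit that number. Its plural reference to mood scores, and its mention under Statistical power of cut-points for each primary outcome variable, lean towards separate scores.

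The pilot purpose also counts. Under Pilot study endpoints the analyses serve as indications of possible benefit, with effect sizes informing later trials. That lowers the consequence of a false positive, but the plan has still chosen a formal corrected threshold, which ought to match what is tested.

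**Conclusion.** The point holds as a mismatch between the stated count of three and the five or six primary scores listed. If each score is read at 0.0167, the overall chance of a false positive is 8.1% (five) or 9.6% (six) under independence, and stays above 5% across the assumed correlations. Mood carries most of the excess, at roughly two to four times its 1.67% share (3.9% to 6.5% over all the cases shown). These figures rest on one test per score and count neither the two post-baseline time points nor the between-group comparisons made in the same models. Severity is moderate: the control of error is not secured as written, but the trial is a pilot and the repair is short.

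**What to change.** Before any outcome data are seen, add one sentence to Planned statistical analyses that takes one of these routes.

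1. Name one mood score as the single test of hypothesis 1 at 0.0167, and label the other mood scores supportive. Three ANCOVAs at 0.05/3 are then correct as written.
2. Define one mood composite, for example the mean of standardised scores with positive affect reversed, and test it at 0.0167, with the individual scores supportive.
3. Keep every score primary and divide by the real count: 0.0100 for five or 0.0083 for six. Alternatively, leave quality of life and sleep at 0.0167 and split mood's share, giving 0.0056 each for three scores or 0.0042 each for four.

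Under route 2 or 3 the sentence should also say whether the PANAS-C gives one score or two; under route 1 this is needed only if the PANAS-C supplies the named score.

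Routes 1 and 2 cost no alpha, but the remaining mood scores lose primary status. Route 3 keeps them all at the price of a stricter threshold, which weighs in a sample with 28 completers targeted. No route changes data collection.

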### Participants

Based on prior studies testing cognitive-behavioral interventions in adolescents with cancer, eligible participants are adolescents aged 11 to 18 years with a diagnosis of cancer
[23-25]. In keeping with previous research, there will be no specific selection/exclusion based on type, stage, or trajectory of cancer
[11,26-28]. The intervention will be conducted in French. Therefore, participants are required to speak and understand the language. They must be willing to participate in an 8-week mindfulness meditation program and be available to complete the measures 6 months after the intervention. They must not have a diagnosis of severe mental illness.

Based on prior mindfulness intervention studies with adolescent populations and on usual number of participants in a mindfulness-intervention training group (as indicated by Kabat-Zinn and colleagues
[29] in the MBSR program) a final sample size of 28 participants is targeted
[13,29-33]. Taking into consideration attrition rates from prior research (20-30%), an additional 12 participants will be recruited
[2,34-36]. Thus, a total of 40 participants will be recruited. Participants will be randomly assigned to the experimental or control group, and immediately given a participant ID for confidentiality and anonymization purposes. Twenty adolescents will be completing the mindfulness meditation intervention, which will be taught by two trained therapists (doctoral clinical psychology student and psychiatrist). The intervention will comprise of eight weekly sessions, lasting 90 min each.

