### Randomization

Participants will be assigned to one of two groups according to a computer-generated randomization list (computerized random numbers). As such, participants will be randomly assigned with a 1:1 allocation ratio following permuted block design procedures, using block sizes of four. No stratification criteria will be used. The allocation sequence will be generated by an independent researcher not involved in this project after baseline measures, thus ensuring that therapists and recruiters are kept blind to the allocation of each participant. The allocation sequence will be password protected and only accessible by the independent researcher. The research assistant responsible for the logistics of this project - who is not part of the treatment team - will not be kept blind for allocation and will be responsible for contacting participants randomly assigned to the experimental condition.

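### A fixed Bonferroni level of 0.0167 for each of the three primary hypotheses is valid, but Holm's step-down procedure keeps the same 5% and never rejects less; the power gain is modest

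*Protocol article*

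**What the plan says.** Under Primary aim, "three hypotheses are formulated", one each for mood, quality of life and sleep, with improvement expected in all three. Planned statistical analyses sets the overall level: "The cut-point to reject the null hypothesis will be set at 5% (α ≤0.05"). It continues: "Primary hypotheses will first be tested using three mixed analyses of covariance (ANCOVA"), "with Bonferonni corrections and individual critical alpha levels at 1.67% (α ≤0.0167"). Each test therefore has its own fixed threshold, whatever the other two show. No step-down, hierarchical or other procedure is named.

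The same section describes the primary tests as intra-group and uses the between-group comparisons for secondary hypotheses. On size, Participants states that "a final sample size of 28 participants is targeted" and that "a total of 40 participants will be recruited"; Randomization allocates 1:1. Statistical power expects small effects and gives no number. The literature review cites moderate effects, also without a number.

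**The concern.** Single-step Bonferroni and Holm's step-down procedure give the same guarantee: at most a 5% chance of any false rejection, whatever the correlation between outcomes. Holm asks less of the second and third p-values once the first has passed. Under the fixed rule, a domain with p between 0.0167 and 0.05 is always declared negative, even when the other two are clearly positive. Under Holm that last domain would be declared at 0.05.

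The difference is largest when several effects are real, and that is what this trial hypothesises. With about 28 completers there is little power to spare. The same section also justifies the mixed ANCOVA partly by its power, so power is a declared aim of the analysis.

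**Working it through.** **The plan's own figure.** 0.05/3 = 0.016667, which rounds to the stated 0.0167. Three independent tests at 0.05/3 give a family-wise error of 1 - (1 - 0.05/3)^3 = 0.0492. The stated level is reproduced and valid.

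**Inputs from the article.** Family-wise level 0.05; three hypotheses, three tests; 28 completers at 1:1, so 28/2 = 14 per group. The recruitment target agrees with this at the upper end of the quoted 20-30% attrition: 28/(1 - 0.30) = 40.

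**Assumptions, because the article gives no figures.** Two-sided tests; d = 0.2, 0.5 and 0.8 for small, moderate and large, equal in all domains; pre-post correlation r = 0.6; cross-domain correlation 0.3-0.5; t-tests in place of the mixed ANCOVA.

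**Holm's rule.** Order p(1) ≤ p(2) ≤ p(3). Compare p(1) with 0.05/3 = 0.0167, p(2) with 0.05/2 = 0.025 and p(3) with 0.05, stopping at the first failure.
- Error control: suppose m0 of the three nulls are true. A first false rejection requires some true null to have p ≤ 0.05/m0. Summed over the m0 true nulls, that probability is at most m0 × 0.05/m0 = 0.05, whatever the dependence.
- Never less: every Holm threshold is at least 0.0167, so each hypothesis that Bonferroni rejects is also rejected by Holm. This held in every simulated trial.

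**Simulated family-wise error** (14 per group, uncorrelated outcomes, 100,000 trials per setting):

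| True state | Bonferroni | Holm |
|---|---|---|
| All three null | 0.049 | 0.049 |
| One very large effect, two null | 0.034 | 0.050 |
| Two very large effects, one null | 0.017 | 0.050 |

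The part of the 5% that Bonferroni leaves unused when some effects are real is what Holm recovers.

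**Mean power per domain, two-arm contrast adjusted for baseline.** The residual SD factor is sqrt(1 - 0.6^2) = 0.8, with 14 + 14 - 2 = 26 df.

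| d | Bonferroni | Holm | Gain |
|---|---|---|---|
| 0.2 | 4.0% | about 4.4% | under 1 point |
| 0.5 | 20% | 24% | 3-4 points |
| 0.8 | 54% | 63% | about 9 points |

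**Intra-group tests, 14 in one group.** The SD of change is sqrt(2 × (1 - 0.6)) = 0.894 of the outcome SD. The gains in mean power per domain are about 0.5-0.7 points at d = 0.2, 6 points at d = 0.5 (about 30% to 36%) and 9-10 points at d = 0.8.

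**Sensitivity, two-arm contrast with no gain from the covariate** (14 per group, cross-domain correlation 0 to 0.5):
- d = 0.2: 3.1% to 3.2-3.4%.
- d = 0.5: 12.7% to 13.8-14.9%.
- d = 0.8: 34.8% to 40.5-41.2%.

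**At least one rejection.** The first rejection needs p ≤ 0.0167 under both rules, so this probability is identical in every setting.

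**The case against.** The strongest reply is that nothing here is wrong. The level is prespecified, the arithmetic is correct and the error control is valid. A reader might infer from this point that the plan's multiplicity control is faulty; the article does not support that, and the point is about efficiency only.

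A reader might also infer that the trial loses a large share of its power. That reading needs d = 0.8 in all three domains at once, where the two-arm chance of declaring all three rises from 23-28% to 42-47%. The article expects small effects, and at d = 0.2 the gain is under 1 point. Nor does it make significance in all three domains a success criterion: Pilot study endpoints uses effect sizes as indicators, alongside recruitment, retention and acceptability. This objection stands, and it limits the size of the point.

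The two-arm figures describe a contrast that the article calls secondary. That is correct, but the gain persists for the intra-group tests.

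Holm also needs one p-value per hypothesis, whereas mood is measured by the two Beck scales and the PANAS-C, each at several time points. This stands too. It applies equally to a Bonferroni divisor of three, and the fix has to deal with it.

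Finally, Bonferroni gives simple simultaneous confidence intervals. The article plans none; it reports partial eta squared and Cohen's d, neither of which depends on the multiplicity rule.

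**Conclusion.** The point holds as a minor efficiency loss. That Holm keeps the family-wise 5% and never rejects less is a mathematical fact and needs no assumption about this trial. The size of the gain does rest on assumptions: the effect sizes, r = 0.6, the cross-domain correlation, 14 per group and t-tests standing in for the mixed ANCOVA. It is negligible at the small effects the article expects, a few points at moderate effects and about 9-10 points at large ones. Holm would not rescue the power of a trial of this size, because the chance of any positive finding is the same under both rules.

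**What to change.** In Planned statistical analyses, replace the fixed 1.67% level by Holm's step-down procedure at a family-wise 5%, with ordered p-values compared with 0.05/3, 0.05/2 and 0.05. Name the single p-value (score and time point or model term) that represents each hypothesis. If mood keeps several scales, apply Holm to the full set of primary scores, with thresholds set by the number of tests. For six scores (two Beck, two PANAS-C, quality of life, sleep) the sequence starts at 0.05/6 = 0.0083 and ends at 0.05, again with one designated p-value per score.

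The cost is one or two sentences, with no extra data and no software beyond the planned SPSS output. Simultaneous intervals matching Holm are less simple. If ordinary 95% intervals are reported, label them as unadjusted, since one may exclude zero where Holm does not reject.

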### Statistical power

Effect sizes will first be calculated using partial eta squared (partial η^2^) in order to evaluate the pre-post effect of the intervention. Cohen’s d will also be calculated in order to evaluate the effect of the intervention between groups. Based on the previous literature on MBSR and oncology, small effect sizes are usually found
[36]. Given the pilot-testing nature of this study, it may be that we will not detect large group differences. In this perspective, clinical significance and cues of intervention success will be evaluated based on individual courses and established cut-points for each primary outcome variable. Participant journals may also be taken into consideration for qualitative information regarding the intervention.

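### The protocol makes pre-post change within the experimental arm the test of its primary hypotheses and the randomised comparison secondary, although its aim is an effect relative to controls

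*Protocol article*

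**What the plan says.** Under Primary aim, the protocol article sets out to evaluate the "effects of a mindfulness-based meditation intervention on quality of life, sleep, and mood in adolescents with cancer compared to a control group". The same section then makes the three hypotheses specific in a different way: "significant improvements are expected to be observed in quality of life, mood, and sleep between pre-intervention and post-intervention measures in the experimental group", with the effect expected to last to 6 months.

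Under Planned statistical analyses, the primary hypotheses are tested with three mixed ANCOVAs, each at 0.0167 after Bonferroni correction. The models adjust for baseline differences between participants in each condition and for possible confounders. Their role is then described: "These intra-group analyses will serve to evaluate the impact of the mindfulness-based meditation intervention" on the three outcome domains. The randomised comparison comes next: "These analyses will also serve to test secondary hypotheses, by allowing inter-group comparisons between the experimental group and the wait-list controls".

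The Statistical power section keeps this order. "Effect sizes will first be calculated using partial eta squared", for the pre-post effect, and between-group Cohen's d is calculated as well. After the wait-list participants have been treated, "Comparable analyses will be conducted on the data collected from the second experimental group". The Abstract also puts intra-group analyses before inter-group ones.

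**The concern.** Randomising to a wait-list separates the effect of the intervention from whatever would have happened anyway. A contrast of pre with post scores inside the experimental arm does not make that separation, so it cannot answer a question framed as a comparison with controls.

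The design leaves room for such change. The Participants section admits any type, stage or trajectory of cancer. The screening section warns of a delay of a few weeks up to a few months before the intervention starts, and baseline measures are taken before that delay. Follow-up then runs for 6 months more. The change could go either way: recovery would be credited to mindfulness, while the deterioration or renewed treatment that the Discussion anticipates would mask a real benefit.

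The analysis of treated wait-list participants has the same weakness. They start only after the experimental group has completed follow-up, so no untreated concurrent group remains.

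**Working it through.** **The plan's own figures.** 0.05/3 = 0.01667, which is the stated 0.0167. Recruitment: 28/(1 − 0.30) = 40, as stated, at the upper end of the 20-30% attrition range. With 1:1 allocation this gives 20 recruited and 14 completing per arm. The article states no power calculation, so there is none to reproduce.

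**Which contrast is primary.** Set side by side:
- Aim: effect compared to a control group.
- Specific expectation: improvement from pre to post in the experimental group.
- Test of the primary hypotheses: mixed ANCOVAs, described as intra-group.
- Comparison with controls: secondary hypotheses.
- Effect size: pre-post first, between-group also.

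Neither a group-by-time interaction nor an adjusted group difference at a named time point is called the deciding test.

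**Illustration of a within-arm contrast.** Assumptions: no intervention effect; both arms improve by a common amount s (in SD units); equal SD at both visits; pre-post correlation r; two-sided test (the article does not state sidedness). The article gives neither s nor r, so both are shown as ranges.

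Standardised paired change: dz = s/√(2(1 − r)). Noncentrality: dz√n, with n − 1 degrees of freedom.

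For n = 14 the critical value at 0.05/3 is 2.746. Example with s = 0.3 and r = 0.5: dz = 0.3/√1 = 0.30; noncentrality = 0.30 × √14 = 1.12; rejection probability 8.3%.

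| Common improvement | n = 14, r = 0.5 to 0.7 | n = 20, r = 0.5 to 0.7 |
|---|---|---|
| 0 | 1.67% | 1.67% |
| 0.2 SD | 4.4% to 6.4% | 5.9% to 9.3% |
| 0.3 SD | 8.3% to 13.6% | 12.5% to 21.5% |
| 0.5 SD | 23.4% to 40.4% | 37.3% to 60.8% |

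At r = 0.6 and n = 14 the values for 0.3 and 0.5 SD are 10.2% and 29.9%. A common deterioration of the same size gives the same rejection rates in the direction of harm.

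**The between-arm contrast under the same conditions.** An ANCOVA of the post score on group, adjusted for baseline, was simulated 20,000 times per setting. It rejected in 1.5-1.7% of runs at every common change tried (0, 0.3 and 0.5 SD), because the shared change cancels.

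**Power of that contrast.** With 14 per arm and r = 0.6, the residual SD is √(1 − 0.36) = 0.8. Noncentrality = d/(0.8 × √(2/14)), with 25 degrees of freedom and a critical value of 2.566. For d = 0.3 the noncentrality is 0.99 and power is about 7%. For d = 0.5 it is 1.65 and power is about 20%.

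**The case against.** The strongest reply is that the named method is a mixed ANCOVA. Such a model normally has a between-subjects group factor, and the wording about participants in each condition implies that both arms are in it. The same analyses are said to serve the inter-group comparison, so the randomised comparison is planned. This stands. A reader might infer that the analysis ignores the control arm altogether, and the document does not support that. What it supports is that the within-arm contrast is labelled primary and the between-arm contrast secondary.

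Three further limits also stand.
- The percentages are for a simple paired test in one arm under assumed drift. They are not the error rate of the planned covariate-adjusted model.
- A reader might add regression to the mean as a built-in source of false benefit. No symptom threshold is set for entry, and the Discussion suggests volunteers may be healthier than average. Regression to the mean is therefore possible but not designed in; natural course is the better supported threat.
- A reader might infer that a pre-post effect size will be used to size the next trial. The article also plans between-group Cohen's d, and it links future sample size estimates to retention and attrition. Effect sizes serve to judge whether variables are worth carrying forward.

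Pilot status lowers the stakes, but it does not settle the point, since the article still plans formal tests of primary hypotheses at a corrected alpha.

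**Conclusion.** The point holds as a fault in the choice of primary contrast. The Primary aim and Planned statistical analyses sections declare a contrast that cannot answer the article's own question, and the Statistical power section follows the same order. Bonferroni correction controls for testing three hypotheses; it gives no protection against change common to both arms.

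The size depends on assumptions. For a within-arm paired test with 14 completers and r of 0.5 to 0.7, false rejection at a nominal 1.67% is about 8-14% for a common improvement of 0.3 SD and 23-40% for 0.5 SD. With no common change there is no inflation, and with deterioration the error runs towards missing a benefit. The conclusion about the contrast does not depend on these values.

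**What to change.** Under Primary aim and Planned statistical analyses, name the between-arm contrast from the model already planned as the primary test of each hypothesis. It can be the baseline-adjusted group difference or the group-by-time interaction, at a stated time point such as 8 weeks. Both post-baseline assessments remain usable for this, because controls are offered the programme only after the experimental group's follow-up. Report within-arm change descriptively for both arms. In the Statistical power section, lead with the between-group effect size and its 95% confidence interval. Label the analysis of treated wait-list participants exploratory, since it has no concurrent control.

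The cost is rewording; no new data or model is needed. The downside is lower apparent significance: power is about 7% for d = 0.3 and 20% for d = 0.5 at 0.0167 with 14 per arm and r = 0.6. The article itself expects small effects. The primary result should therefore be presented as an estimate with its interval, and a non-significant test should not be read as absence of effect.
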